### Study design

2.1

This study is a single-center, three-arm parallel explanatory randomized controlled trial conducted in China (Figure 1). A total of 96 patients with LDH will be recruited and randomly allocated in a 1:1:1 ratio to the Tuina group, the core stability training group, or the combined intervention group. Participants who meet the inclusion criteria will be enrolled after providing written informed consent. Participants will be recruited from 15 October 2025 to 1 November 2027 through outpatient clinics, public advertisements, and social media platforms. All three groups will receive an 8-week intervention, administered three times per week, followed by a 1-month follow-up period. Outcome assessments will be conducted at baseline, after 8 weeks of intervention, and at the end of the follow-up period. The intervention duration was determined based on dose–response evidence, direct clinical trials, and prior rehabilitation literature. A recent systematic review and meta-analysis on stabilization-based exercise in patients with chronic low back pain reported that 8–12-week interventions produced the greatest effects on pain reduction (SMD = –0.88) and disability improvement (SMD = –0.85), with high-certainty evidence for disability outcomes (21). Consistent with this evidence, randomized controlled trials in patients with LDH have commonly adopted 8-week core stabilization protocols. An 8-week motor control training program significantly improved pain, disability, and transversus abdominis activation (22), while an 8-week program (three sessions per week) also demonstrated significant improvements in pain, disability, and trunk muscle endurance (23). Accordingly, an 8-week intervention period was selected, representing a commonly adopted duration within the evidence-supported 8–12-week therapeutic window for stabilization-based interventions in LDH. A 1-month follow-up assessment was included to evaluate the short-term maintenance of treatment effects after completion of the intervention, which is consistent with early post-intervention assessment time points used in randomized controlled trials of LDH (24). To enhance methodological rigor and minimize potential bias, blinded outcome assessment and statistical analysis procedures were incorporated into the study design. Outcome assessment and statistical analysis will be performed by two independent researchers who are blinded to group allocation. The primary and secondary outcome measures include musculoskeletal ultrasound, imaging assessments, pressure biofeedback unit assessment, and patient-reported clinical outcomes to comprehensively assess lumbar stability, pain, and functional status. The study protocol was developed in accordance with the SPIRIT guidelines, and the completed SPIRIT checklist is provided as Supplementary Table S1. In addition, a treatment fidelity checklist is provided as Supplementary Table S2 to ensure consistency and quality of intervention delivery.

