### Outcomes

2.7

The efficacy evaluation in this study will focus on the primary and secondary outcome measures assessed at baseline and immediately after the intervention. In addition, selected clinical outcomes, including pain intensity and functional status, will be reassessed at the 1-month follow-up using the VAS and ODI to evaluate the persistence of treatment effects. Follow-up assessments will be conducted by independent outcome assessors who are blinded to group allocation.All outcome assessments will be conducted by independent researchers who are blinded to group allocation and are not involved in other aspects of the study. The schedule of enrolment, interventions, and assessments is presented in (Figure 5).

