#### Primary outcome

2.7.1

The primary outcome is the muscle activation ratio of the transversus abdominis (TrA) assessed by musculoskeletal ultrasound, which reflects the neuromuscular control capacity of the deep core musculature. The muscle activation ratio is calculated as follows:

$$\begin{array}{l} \text{Activation ratio}=\frac{\text{muscle thickness duringcontraction}}{\text{muscle thickness at rest}} \end{array}$$

This measure has been widely used as an indicator of deep core muscle activation.

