##### Musculoskeletal ultrasound assessment

2.7.1.1

Before and after the intervention, musculoskeletal ultrasound examinations will be performed using a Siemens Sequoia Silver ultrasound system (probe frequency: 5–12 MHz). The external oblique (EO), internal oblique (IO), transversus abdominis (TrA), and lumbar multifidus muscle (LMM) will be assessed in both groups. For EO, IO, and TrA measurements, the probe will be positioned at the level of the umbilicus along the mid-axillary line. The LMM will be located approximately 2 cm lateral to the L4 spinous process. Muscle thickness will be measured under standardized tasks: active straight-leg raising of the right lower limb in the supine position will be used for EO, IO, and TrA assessment, while single-leg standing on the left lower limb in the upright position will be used for LMM assessment. For each muscle, thickness will be measured three times at rest, at the end of standardized inspiration, and at the end of standardized expiration, and the mean value will be recorded. The muscle activation ratio will be calculated as the ratio of muscle thickness during contraction to that at rest. All measurements will be performed by an experienced sonographer. A subset of measurements will be repeated to assess intra-rater reliability.

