### Statistical analysis

2.11

All statistical analyses will be performed using IBM SPSS Statistics (Version 27.0). Efficacy analyses will follow the intention-to-treat (ITT) principle, including all randomized participants. Continuous variables will be tested for normality and presented as mean ± standard deviation or median (interquartile range), as appropriate, while categorical variables will be expressed as counts and percentages. Baseline characteristics will be summarized descriptively without formal statistical comparisons. Primary and secondary outcomes will be analyzed using linear mixed-effects models, with group, time, and group-by-time interaction as fixed effects and subjects as random effects. Intervention duration (20 vs. 40 min) and baseline values of the outcome measures will be explicitly included as covariates to account for potential confounding effects. Therapist identity will be included as a random intercept to account for potential clustering effects. Model assumptions will be evaluated using residual diagnostics. If significant group-by-time interactions are detected, post-hoc pairwise comparisons with Bonferroni correction will be performed. Missing data will be handled using multiple imputation under the missing-at-random assumption. Safety analyses will include all participants who received at least one treatment, and adverse events will be compared using the chi-square test or Fisher's exact test, as appropriate. Sensitivity analyses, including complete-case analyses, per-protocol analyses, and analyses adjusted for intervention duration, will be conducted to assess the robustness of the primary outcome. All statistical tests will be two-sided, with a significance level set at *P* < 0.05, and 95% confidence intervals will be reported. Effect sizes (e.g., Cohen's d) will also be reported to facilitate interpretation of the clinical relevance of the findings.

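### For outcomes measured only before and after treatment, including the primary one, the stated mixed model must use baseline as both response and covariate, which makes the standard error of the group-by-time test too small

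*Protocol article*

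**What the plan says.** Section 2.11 (Statistical analysis) gives one model for all primary and secondary outcomes: "linear mixed-effects models, with group, time, and group-by-time interaction as fixed effects and subjects as random effects". In the same model, "baseline values of the outcome measures will be explicitly included as covariates to account for potential confounding effects". The treatment comparison runs through the interaction: "If significant group-by-time interactions are detected, post-hoc pairwise comparisons with Bonferroni correction will be performed".

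The endpoint is fixed in 2.7.1: "The primary outcome is the muscle activation ratio of the transversus abdominis (TrA) assessed by musculoskeletal ultrasound". Its timing is in 2.7.1.1: "Before and after the intervention, musculoskeletal ultrasound examinations will be performed". Section 2.7 agrees. It places the primary and secondary outcomes at baseline and directly after treatment, and then says that "selected clinical outcomes, including pain intensity and functional status, will be reassessed at the 1-month follow-up using the VAS and ODI". Section 2.1 is broader and does not separate outcomes: "Outcome assessments will be conducted at baseline, after 8 weeks of intervention, and at the end of the follow-up period".

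**The concern.** On the outcome-specific sections, the primary outcome has one post-baseline visit. A time factor, a group-by-time term and a separable subject effect then need baseline as one of the two response rows. The stated covariate is that same baseline value, so the model regresses baseline on itself. If baseline is taken out of the responses, time and the interaction disappear and the subject effect cannot be told apart from residual error. Neither reading of 2.11 gives a sound model for this outcome.

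At stake is the test that opens every pairwise comparison, including combined treatment against each single treatment, which is the trial's question. The same holds for the other outcomes that 2.7 does not carry to 1 month: the other ultrasound measures, imaging, PBU, JOA and SF-36. The sensitivity analyses in 2.11 (complete-case, per-protocol, duration-adjusted) are not described as changing the role of baseline.

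**Working it through.** **Inputs from the protocol.** Three arms at 1:1:1; d = 0.78; two-sided alpha 0.05; power 0.80; 27 per arm; 15% dropout; 32 per arm and 96 in total (2.5). Two visits for the primary outcome (2.7, 2.7.1.1).

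**Inputs assumed.** The baseline-to-week-8 correlation rho is not given, so it is varied from 0 to 0.85. Data are normal, with equal SDs at the two visits unless stated. The duration covariate and the therapist intercept were left out of the check. Both are constant over a participant's visits and so do not enter the change contrast.

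**The plan's own figure.** A two-sample t-test with d = 0.78 has power 0.788 at 26 per arm and 0.803 at 27. Then 27/0.85 = 31.8, so 32 per arm and 96 in total. The sample size reproduces and is not affected by this point.

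**Algebra (variance SD² at each visit).**
1. The covariate is the same at both visits, so its slope is that of the participant's two-visit mean on baseline: (1+rho)/2.
2. The residuals are y0·(1−rho)/2 at baseline and y1 − y0·(1+rho)/2 at week 8.
3. Their covariance is −SD²(1−rho)²/4, negative for every rho below 1. A random-intercept variance cannot be negative, so it is estimated at zero.
4. With no subject variance, the model uses the average residual variance, SD²(1−rho)(3+rho)/4. The change contrast needs SD²(1−rho).
5. The ratio of model SE to true SE is therefore sqrt((3+rho)/4).
6. The interaction estimate is the difference in mean change, with variance 4·SD²(1−rho)/n. ANCOVA has 2·SD²(1−rho²)/n. The ratio is 2/(1+rho).

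**Simulation under no effect (27 per arm, 12,000 trials per setting, REML).**

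| rho | SE ratio, formula | SE ratio, simulated | Subject variance at zero | Omnibus type I error, with covariate | Omnibus, no covariate | Pairwise, with covariate | Pairwise, ANCOVA | 2/(1+rho) |
|---|---|---|---|---|---|---|---|---|
| 0 | 0.866 | 0.876 | 100% | 10.6% | 4.9% | 8.6% | 4.8% | 2.00 |
| 0.3 | 0.908 | 0.910 | 100% | 8.5% | 4.9% | 7.8% | 5.0% | 1.54 |
| 0.5 | 0.935 | 0.938 | 100% | 7.4% | 5.0% | 6.7% | 4.9% | 1.33 |
| 0.7 | 0.962 | 0.959 | 99.5% | 6.5% | 5.0% | 6.5% | 5.1% | 1.18 |
| 0.85 | 0.981 | 0.987 | 93% | 5.5% | 4.7% | 5.4% | 4.8% | 1.08 |

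At 32 per arm and rho 0.5 the omnibus error is 7.6%. With the week-8 SD 1.3 times the baseline SD and rho 0.5, the SE ratio is 0.97 and both the omnibus and the pairwise error are 6.2%.

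**Direct fit.** In one simulated data set fitted with a standard mixed-model routine, the interaction estimate was 0.0428 with and without the covariate, while its SE fell from 0.273 to 0.254. The covariate changes only the stated precision.

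**Power (normal approximation, 27 per arm, d = 0.78 in SD units of the outcome).** The noncentrality is 0.78/sqrt(2/27) = 2.87, divided by sqrt(1−rho²) for ANCOVA and by sqrt(2(1−rho)) for the change contrast with a correct SE. ANCOVA against change gives 0.85 against 0.68 at rho 0.3, 0.91 against 0.82 at rho 0.5, and 0.98 against 0.96 at rho 0.7.

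**Three visits.** For an outcome with baseline, week-8 and 1-month values and equal correlations, the same double use of baseline gave an SE ratio of about 1.00 and type I error of 4.7–5.1%.

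**The case against.** The protocol nowhere says that baseline is a level of time. That is right, and for VAS and ODI the wording of 2.11 also describes a standard, valid model: week-8 and 1-month responses with baseline as covariate. A reader might infer that the model fails for every outcome. The documents do not support that, and no SE deficit was found with three visits. For two-visit outcomes, however, baseline as a response is the only way to fit the stated terms.

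The deficit also depends on the variance of a random intercept being bounded at zero. A compound-symmetry residual that allows negative covariance brought the interaction test back to 4.9%, 4.9%, 5.1% and 4.6% at rho 0.3, 0.5, 0.7 and 0.85 (6,000 runs). A separate analysis plan could choose that structure, but 2.11 names subjects as random effects, which points to a random intercept.

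The size is moderate. With the Bonferroni step behind the gate, family-wise error was 7.6%, 6.4%, 5.6% and 4.6% at the same four correlations for interaction contrasts, and 8.3%, 7.3%, 6.4% and 5.3% for week-8 group comparisons. This tempers the size but does not remove the conflict.

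A reader might also conclude that the analysis takes no precision from baseline. That is true only of the added covariate. The change contrast already uses baseline and beats a comparison of week-8 values alone when rho exceeds 0.5. Being less precise than ANCOVA is a loss of efficiency, not an error.

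Finally, 2.1 could mean that ultrasound is repeated at 1 month, and the schedule figure is not shown. If so, two post-baseline responses would exist and the stated model could be fitted with baseline as covariate only. Sections 2.7 and 2.7.1.1 are more specific and say otherwise, but the conflict is for the sponsor to resolve.

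**Conclusion.** The point holds for the primary outcome and for every other outcome measured only before and after treatment. As written, the model can be fitted to them only with baseline in both roles. With the stated random subject effect, the SE of the group-by-time contrast is then about 9%, 6%, 4% and 2% too small at rho 0.3, 0.5, 0.7 and 0.85, with the omnibus error rates shown in the table. These sizes rest on an assumed rho, equal SDs, normal data and a random intercept bounded at zero. They shrink as rho rises or if the week-8 SD is larger. The covariate brings no real gain for the interaction estimate. The point does not extend to the standard errors for VAS and ODI, and it does not show that the sample size is wrong. It still needs correcting, because it concerns the test that gates all pairwise comparisons.

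**What to change.** Do not use baseline in both roles.

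- **Two-visit outcomes, including the primary:** ANCOVA of the week-8 value on group and baseline, with the week-8 group contrasts named as the primary test. An equally valid choice is to keep baseline as a response, drop it as a covariate and constrain the group means to be equal at baseline.
- **VAS and ODI:** state that the week-8 and 1-month values are the responses and that baseline is a covariate.
- **Visits:** reconcile the general three-visit sentence in 2.1 with 2.7 and 2.7.1.1, so that it is clear which outcomes are measured at 1 month. If ultrasound proves to be among them, the VAS and ODI form can serve for it too.

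The cost is wording in 2.11 and 2.1. No added patients or data are needed. With ANCOVA, type I error is about 5%, and the variance is (1+rho)/2 of that of the planned contrast: 0.65 at rho 0.3, 0.75 at 0.5 and 0.85 at 0.7.

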#### Inclusion criteria

2.2.1

Diagnosis of lumbar disc herniation (LDH) according to established diagnostic criteria (25), confirmed by MRI showing disc protrusion, extrusion, or sequestration at L3/4, L4/5, or L5/S1 levels. Mild-to-moderate degenerative changes (Pfirrmann grade ≤ III) in the absence of significant nerve root compression do not exclude participation.Age ≥ 20 and ≤ 55 years, regardless of sex (3, 26).Duration of the disease ≥ 3 months (27, 28).Visual Analog Scale (VAS) score ≥ 3 and ≤ 6 (29).Provision of written informed consent, voluntary agreement to participate, and ability to comply with the treatment protocol.

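### The mixed model needs baseline as a time level yet also enters it as a covariate; if baseline VAS is a response, one subject effect misstates the standard errors of post-treatment arm differences

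*Protocol article*

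**What the plan says.** Under Statistical analysis, the primary and secondary outcomes share one linear mixed model, "with group, time, and group-by-time interaction as fixed effects and subjects as random effects". The same paragraph adds that "baseline values of the outcome measures will be explicitly included as covariates" and that "Therapist identity will be included as a random intercept to account for potential clustering effects". No residual covariance structure is named, and the text does not say whether baseline is a level of time. On checking it says "Model assumptions will be evaluated using residual diagnostics", with no stated consequence. Arm comparisons are conditional: "If significant group-by-time interactions are detected, post-hoc pairwise comparisons with Bonferroni correction will be performed".

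Under Study design, "Outcome assessments will be conducted at baseline, after 8 weeks of intervention, and at the end of the follow-up period". The Outcomes section narrows this: VAS and ODI are the measures named for the third visit ("will be reassessed at the 1-month follow-up using the VAS and ODI"), while the ultrasound and imaging sections describe measurement before and after the intervention only. Inclusion criteria require "Visual Analog Scale (VAS) score ≥ 3 and ≤ 6". The Patient-reported outcomes section puts VAS on a 0–10 scale. No entry limit is set for ODI.

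**The concern.** There are two linked problems.

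- **Baseline has two roles.** For the ultrasound primary outcome, removing baseline from the responses leaves one visit, so neither time nor group-by-time can be estimated. The model as written therefore needs baseline as a level of time. The text nevertheless also lists baseline as a covariate.
- **One variance is imposed on VAS.** Read literally, a subject random intercept gives every visit the same variance and every pair of visits the same correlation. Baseline VAS is confined by the entry window and later VAS is not. If baseline is a response row, its restricted variance is averaged into the error used for week 8 and month 1.

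At stake are the standard errors and 95% intervals for VAS arm differences after treatment. VAS is one of the two outcomes on which the plan rests its assessment of persistence.

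**Working it through.** **Inputs from the document.** Three visits for VAS; entry range 3–6; scale 0–10; 32 per arm. The plan gives no figure for the VAS model. Its sample size does reproduce: d = 0.78 at two-sided 0.05 gives power 0.788 with 26 per arm and 0.803 with 27; 27/0.85 = 31.8, so 32 per arm and 3 × 32 = 96.

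**Assumptions, because the document gives no SDs or correlations.** Baseline VAS spread evenly over 3–6 has SD 3/√12 = 0.87; the maximum, with half at each end, is 1.5. Later SD is varied from 0.7 to 2.1, the baseline–later correlation from 0.3 to 0.5, and the week 8–month 1 correlation is 0.7 unless stated. The therapist intercept and the duration covariate are left out; neither frees the visit variances.

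**Case A: baseline is a response and not a covariate.** In a balanced random-intercept fit, the variance used at each visit tends to the mean of the visit variances. For a post-treatment arm difference,

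model SE / true SE = √[(s₀² + 2s₁²)/3] / s₁,

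with s₀ the baseline SD and s₁ the later SD. Example: s₀ = 0.87, s₁ = 1.5 gives √[(0.757 + 4.5)/3]/1.5 = 1.324/1.5 = 0.88. The true size of a nominal 5% test is 2[1 − Φ(1.96 × ratio)], here 2[1 − Φ(1.73)] = 8.4%.

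| Baseline SD | Later SD | SE ratio | True size of 5% test |
|---|---|---|---|
| 0.87 | 0.7 | 1.09 | 3.3% |
| 0.87 | 0.87 | 1.00 | 5.0% |
| 0.87 | 1.2 | 0.92 | 7.2% |
| 0.87 | 1.5 | 0.88 | 8.4% |
| 0.87 | 1.8 | 0.86 | 9.1% |
| 0.87 | 2.1 | 0.85 | 9.5% |
| 1.1 | 1.3 | 0.95 | 6.2% |

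Simulated null trials (32 per arm, 20,000 per setting) agree:

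- SDs 0.87/1.5/1.5, correlations 0.4 and 0.7: ratio 0.88, size 8.1%.
- SDs 1.0/1.8/1.8, correlations 0.3 and 0.8: ratio 0.875, size 8.6%.
- SDs 1.1/1.3/1.3, correlations 0.4 and 0.6: ratio 0.95, size 6.0%.
- Equal SDs: ratio 1.00, size 5.1%.

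An unstructured covariance brought the size to 4.8–5.3% in every setting.

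Other contrasts are affected differently. At baseline SD 0.87, the SE ratio for an arm difference in change from baseline is 0.88–0.97. For change from week 8 to month 1 it is 1.08–1.53, so that SE is too large.

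**Case B: baseline is both response and covariate.** Simulation gives ratios of 0.80–0.90 and sizes of 8–11%. With equal SDs of 1.8, so no effect of the entry window, the ratio is still 0.86 and the size 9%. Here the double use itself does damage.

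**Case C: week 8 and month 1 are the responses and baseline is a covariate.** Ratios are 0.98–1.02 and sizes 4.3–5.7%, even with one common variance.

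**The case against.** The strongest objection is that adjusting for baseline normally means that only post-treatment visits are responses. That is Case C, where nothing is wrong. This stands as far as it goes, and the point is conditional for that reason. But one model is stated for all outcomes, and under Case C its time terms cannot be estimated for outcomes with a single post-treatment visit. The interaction gate also fits Case C poorly: a benefit of equal size at week 8 and month 1 produces no interaction between those visits.

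A second objection is that an article may leave the residual covariance to an analysis plan, and that residual diagnostics could show unequal variances. It is fair that the structure is unnamed rather than fixed as compound symmetry, so that omission alone is no finding. The conflict over the role of baseline is in the text itself, and the diagnostics have no stated consequence.

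Three stronger readings are tempting, and the document does not support them:

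- **That VAS standard errors are always too small.** This needs a later SD above the baseline SD, and no SDs are given. Patients enter at 3–6 on a scale bounded at 0, so a floor effect could reduce later variance and reverse the direction.
- **That ODI is affected in the same way.** ODI has no entry window, so this argument gives no reason for a restricted baseline variance.
- **That VAS benefits would be declared too often under the planned procedure.** The sizes above are for an ungated, unadjusted contrast. With the interaction gate and Bonferroni, and no arm differences at all, simulations put the chance of any false week-8 claim at about 1–4%.

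**Conclusion.** The point holds in conditional form. The model description gives baseline two incompatible roles, and this reaches the primary outcome as well. The variance argument concerns VAS, a secondary outcome.

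If baseline VAS is a response and not a covariate, a subject random intercept makes the standard errors of post-treatment arm differences about 5–15% too small for assumed later SDs of 1.2–2.1 with baseline SDs near 0.9–1.1. On the table's figures, nominal 95% intervals then cover about 90.5–94%. At a later SD of 0.7 against a baseline SD of 0.87, the standard error is 9% too large. If baseline is only a covariate, the error is absent. The harm is mainly misstated intervals, which the gate and Bonferroni do not repair, rather than excess false claims. The SDs and correlations are assumptions, and the gated figures apply to complete absence of arm effects.

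**What to change.** Use baseline in one role only, by either route:

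- **(a) Baseline as a response.** Drop it as a covariate. For VAS, and for ODI for consistency, use a repeated visit effect with unstructured residual covariance and Satterthwaite degrees of freedom.
- **(b) Baseline as a covariate.** Model only week 8 and month 1, with the same unstructured covariance, and test the arm contrast at each visit instead of gating on group-by-time. Outcomes with one post-treatment visit then reduce to a baseline-adjusted comparison at week 8.

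Adding the unstructured covariance while keeping both roles will not work. As the baseline slope approaches 1, the residual of the baseline row shrinks to zero and the likelihood rises without limit.

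The cost is a sentence or two in the analysis section. Route (a) has six variance and covariance parameters for three visits and route (b) three for two, against two for a random intercept with residual variance. Intervals may be slightly wider.
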